#### Microbiota

##### Maternal gut microbiota

All participants will receive written information (Supplement 8) and be instructed on the procedure for collection and storage of the first stool passed in the day at Baseline, Day 10, Day 56- and one-week post-partum. Each participant will be provided with a cooler and ice bricks for storage and transportation of stool samples. Upon receipt, stools samples will be weighed to the nearest 0.1 g on an electric balance (A&D, Japan) then immediately stored in a − 80 °C freezer. Stools will be thawed at 4 °C then homogenized and aliquoted, then restored at − 80 °C until analysed for microbial composition and their SCFA metabolites. This procedure will be repeated for each time point.

Microbial analyses will be performed at the Western Australian Human Microbiome Collaboration Centre at Curtin University. DNA will be extracted using the QIAamp PowerFecal Pro DNA kit (Qiagen). Microbiome signatures will be generated using the Illumina MiSeq platform barcoded V4 primer (515–806) targeting a hypervariable region of the 16S rRNA gene. Polymerase chain reaction free (PCR-free) ligation protocol will be deployed for library building. Samples will be sequenced to a depth of a minimum 20,000 reads, which is sufficient to identify microbes to a genus/species level. Quality control samples and mock communities will be included in the analysis from sample collection to sequence analysis. Sequence read quality will initially be assessed with FastQC before demultiplexing and pre-processing by GHAPv2, an in-house tool. Cutadapt [53] will be used for the removal of all non-biological sequences. DADA2 [54] will then be used for quality filtering, error correction, amplicon sequence variants (ASVs) picking. A trained Naïve Bayes classifier will then assign ASVs to genus/species against a curated database of microbial reference sequences such as the Ribosomal Database Project (RDP) [55] or Genome Taxonomy Database [56].

An increase in RS consumption is known to alter the gut microbiota in non-GDM populations [37]. An alteration from Baseline in stool microbial composition in RS groups towards a symbiotic composition compared with the control group will indicate that the increased RS consumption affects the microbiota of a woman with GDM and would indicate compliance with the RS dietary intervention.

##### Neonatal gut microbiota

A neonatal stool sample will be collected one-week post-partum for microbial analysis as above. These will be used to evaluate the effect of RS supplementation on microbiome seeding of the infants in relation to the maternal microbial composition. The neonatal sample will be collected and stored by the mother at home as per a standard procedure that will be provided with the stool sample kits before discharge (Supplement 9). In brief, the lid of the stool sample pot will contain an integrated scoop that is used to collect the majority of the neonate’s stool sample from the nappy. The sample pot will be capped with the filled scoop, placed immediately into a cooler lined with ice bricks and delivered to the hospital within 24-h. It will be weighed and stored at − 80 °C immediately.

##### Breast milk microbiota

If the mother has chosen to breastfeed, a 10 ml breast milk sample will be collected at one-week post-partum for microbial analysis. A standard procedure and collection tubes will be provided before discharge (Supplement 10). Briefly, after breastfeeding her infant, washing hands with soapy water and donning gloves, the mother will express breastmilk into two 5 ml sterile tubes from the same breast by hand or using a sterilised breast pump. Approximately 3–4 ml will be collected in each tube. Breastmilk samples will be frozen at home then delivered to the hospital in a cooler with ice bricks and immediately stored at − 80 °C until analysis for microbial composition at the Western Australian Human Microbiome Collaboration Centre at Curtin University. The microbiota of breast milk is postulated to be a determinant of the neonatal microbiota [57].

#### Faecal SCFA

The maternal stool samples collected, processed and stored as outlined above at Baseline, Day 10, Day 56 and one-week post-partum will be analysed for concentrations of SCFA (acetate, butyrate and propionate). The method of analysis will use gas chromatography and mass spectrometry as detailed by Stinson, Boyce [58]. An increase from Baseline in mean SCFA is a marker of increased gut microbiota fermentation. SCFA are thought to be the primary metabolites by which the microbiota affects glycaemic control [19–21, 59–62]. Neonatal stool samples collected at one-week post-partum will also be analysed for SCFA content using the above method.

#### Anthropometric measurements

Maternal height will be measured (to the nearest 0.1 cm) by a trained nurse at Baseline using a stadiometer (Seca, Germany). Weight will be measured (to the nearest 0.1 kg) at Baseline, Day 10 and Day 56 using scales (A & D Medical, Japan). Excessive gestational weight gain compromises maternal glycaemic control and therefore it is important to ensure this does not differ between groups.

The birth weight of the neonates’ will be measured to the nearest 5 g by a trained midwife using the scales of a Panda Warmer (General Electric Healthcare, USA). Length at birth will be measured to the nearest centimetre using a metric tape measure. Anthropometric data will be collected from the DMR of the neonates to determine the mean birth weight, Ponderal Index [weight (g) ÷ length (cm)^3^] and percentage of LGA or macrosomic neonates of the intervention groups (RS Diet & RS Supp) compared to the control group. High birth weights are associated with shoulder dystocia, caesarean section delivery, post-partum haemorrhage, childhood obesity, and insulin resistance [63] and therefore one of the main complications of GDM that all treatments aim to improve.

#### Gastrointestinal tolerance

##### Bowel symptoms questionnaire

Mild gastrointestinal side effects are expected with a high consumption of RS. A GI symptoms questionnaire adapted from Francis [64] will be administered at Baseline, Day 10 and Day 56 (Supplement 11). The questionnaire contains a visual analogue scale between 0 and 100 for each of four symptoms, generating a total score of up to 400. Participant responses will be measured manually from the zero mark by the PI and converted to a score out of 100. Scores will be used to evaluate the effect of the interventions on GI comfort and function.

##### Bowel symptoms record

Participants will be asked to keep a bowel symptoms diary at Baseline (Day 1 to 3), Days 8 to 10 and Days 54 to 56 to assess tolerance of the diet and supplement (Supplement 12). This will be returned at the Day 10 and Day 56 study visits. They will record the frequency of bowel movements, rate each movement on a scale of 1 to 7 for consistency using the Bristol Stool Chart [65] and ease of stool passage on a scale of 1–5 where 1 = very easy and 5 = very difficult [66]. The diary includes a subjective scoring of symptoms of flatulence, borborygmus, abdominal cramping and distention, nausea, diarrhoea, constipation. Scores will be chosen from a scale of 0 to 3, where 0 is for no symptoms beyond their normal and 3 is a rating of severe symptoms, an evaluation method used previously by other researchers [67]. The average composite score for individuals’ first 2 days prior to the intervention will be compared to the average score for the second week of the study to establish whether there is a statistically significant difference within individuals and between groups. Scores for individual symptoms will be similarly complied to compare differences within individuals and between groups. This scoring system will also be used as one mechanism for identifying and rating adverse events (AE), along with participants self-reporting of AE. A score of 3 (severe) will be considered an AE and reported in the publications resulting from this trial. A small feasibility study in women with prediabetes or diet controlled T2DM (*n* = 10) trialled the high RS diet and the RS supplement and they were well tolerated (unpublished data). Participants will be encouraged to report any AE to the PI who will escalate to the appropriate health care professional and human ethics committee immediately.

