#### RS supplement

The RS Supp group will consume an RS supplement of high-amylose maize (HAMS) type 2 resistant starch. Participants will be given a 600 g tub of HAMS each fortnight, along with a 40 ml scoop. They will be instructed and provided with written material (Supplement 7) on how to prepare and incorporate the RS supplement into cool fluids or foods in their diet. As with all low-digestible carbohydrates, gastrointestinal (GI) discomfort is a known side effect of rapid introduction of RS, therefore, participants will introduce HAMS over a two-day adjustment period. They will be instructed to consume 1 scoop (20 g) per day for 2 days, taking half in the morning and the rest at night. Then, increasing to a dose of 1 scoop (20 g) morning and night for the remainder of their pregnancy. The RS supplement contains 40% RS type 2. The final amount of RS in the 40 g of HAMS per day will be 16 g, which is below the level of 45 g per day of RS supplementation that is known to be tolerated with minimal side effects, most of which are flatulence [48]. Intakes of up to 80 g RS per day have been tolerated without diarrhoea [48]. Those in the high RS diet plus RS supplement are unlikely to achieve this amount. Consumption and compliance of the RS supplement will be monitored by weight of unconsumed HAMS returned fortnightly. Participants will use a daily RS supplement diary to record intake as an additional measure of compliance. We have shown in a recent 2-week feasibility study, 100% compliance with consumption of the RS supplement and minimal GI side effects in 10 female participants with prediabetes or T2DM (unpublished). GI tolerance of the supplement will be measured via a daily bowel symptom diary for the first 10 days and Days 47 to 56.

Participants can withdraw from the study at any time for any reason. Participants will be withdrawn by the investigator if they commence antibiotics, steroids, metformin or if they can no longer comply with the study’s schedule of assessments (Table 1).

**Table 1 Tab1:** Participant measurements and collection summary

	Day 1	Day 3	Day 10	Day 28	Day 42	Day 56	Day 7 post-partum
Recruitment & consent	√						
Randomisation of subjects	√						
Attend clinic	√	√	√		√	√	
Self-monitoring blood glucose data collection		√	√			√	
FreeStyle Libre Pro application	√				√		
Questionnaires:							
medical Hx	√						
medication	√						
GI symptoms	√		√			√	
Quality of Life SF36	√		√			√	
Weight measured	√		√			√	

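### The bowel symptom diary has two incompatible recording schedules; under the shorter one, the rule that makes a severe score an adverse event cannot operate on Days 4–7 or 47–53

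*Protocol article*

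**What the plan says.** Two sections of the protocol article set the days on which the diary is kept.

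- **RS supplement** (under Intervention): GI tolerance of the supplement is to be "measured via a daily bowel symptom diary for the first 10 days and Days 47 to 56".
- **Bowel symptoms record** (under Gastrointestinal tolerance): participants are to "keep a bowel symptoms diary at Baseline (Day 1 to 3), Days 8 to 10 and Days 54 to 56". The stated purpose is tolerance of both the diet and the supplement.

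The second section also gives the diary a safety role: "This scoring system will also be used as one mechanism for identifying and rating adverse events (AE), along with participants self-reporting of AE". The threshold is explicit: "A score of 3 (severe) will be considered an AE and reported in the publications resulting from this trial".

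For analysis, the mean composite score of the first two days, before the intervention, is to be "compared to the average score for the second week of the study".

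Table 1 shows when diaries are handed in (Days 3, 10 and 56), not which days they cover. The Dietary intervention section starts the high-RS education on Day 3, after baseline data are collected, and Table 1 puts the supplement instructions on the same day. The RS supplement section names GI discomfort as a known effect of introducing RS quickly, and for that reason sets a two-day adjustment period before the amount is increased.

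**The concern.** One instrument has two explicit sets of recording days. This is not an article leaving detail to a fuller document, because both passages are specific and they disagree.

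The days in dispute matter. Four of them, Days 4–7, come directly after the RS diet and supplement start, which is when the protocol itself expects discomfort from rapid introduction. A score of 3 can be recorded only on a day when the diary is open. On Days 4–7 the shorter schedule therefore leaves self-report as the only route by which a severe symptom reaches the AE count. Control women have no RS introduction, so any loss on those days would probably fall mainly on the two RS arms. Tolerance is one of the things a reader will want to know about this intervention.

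**Working it through.** No stated figure needs reproducing; the check is a comparison of day sets.

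**Inputs**

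- Schedule A (RS supplement section): Days 1–10 and 47–56.
- Schedule B (Bowel symptoms record section): Days 1–3, 8–10 and 54–56.
- Start of the RS diet and supplement instructions: Day 3 (Dietary intervention section; Table 1).
- Supplement adjustment period: two days (RS supplement section).

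**Step 1: size and overlap**

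- A: 10 + 10 = 20 days.
- B: 3 + 3 + 3 = 9 days, all of them within A.
- In A but not in B: Days 4–7 (4 days) and Days 47–53 (7 days), so 4 + 7 = 11 = 20 − 9.

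**Step 2: coverage after the start of RS**

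Day 3 is ambiguous: it is labelled Baseline in the diary section but is also the day the intervention begins. Both readings are shown.

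| Window | Days | Recorded under A | Recorded under B |
|---|---|---|---|
| Days 3–10 | 8 | 8 | 4 (Days 3, 8, 9, 10) |
| Days 4–10 | 7 | 7 | 3 (Days 8, 9, 10) |

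Either way, B omits four consecutive days, 4–7. If the supplement is first taken on Day 3, the adjustment period is Days 3–4 and the increase falls on Day 5. Of Days 3–7, B then records only Day 3.

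**Step 3: illustration of what the diary could miss**

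The document gives no rate of severe symptoms. Assume, for illustration only, a constant and independent daily probability p of a score of 3. The chance that the diary records at least one such score in Days 3–10 is 1 − (1 − p)^8 under A and 1 − (1 − p)^4 under B.

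| Assumed p | A (8 days) | B (4 days) |
|---|---|---|
| 0.01 | 7.7% | 3.9% |
| 0.02 | 14.9% | 7.8% |
| 0.05 | 33.7% | 18.5% |

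These figures describe capture by the diary, not by the whole AE system. Clustering of symptoms at introduction would widen the gap, and later onset would narrow it.

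**Step 4: can schedule A apply to the RS Supp arm only?**

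Schedule A appears in the supplement section, so this is worth testing. Schedule B covers all participants and explicitly includes the supplement, so RS Supp women would still have two schedules. If A nevertheless applied to them alone, the score-3 rule would run over 20 days in RS Supp and 9 days in RS Diet and Control, and the counts would not be comparable across arms.

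**Step 5: the second-week comparison**

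Counting from Day 1, the second week is Days 8–14. Both schedules record Days 8, 9 and 10 of it, 3 of 7 days. This looseness is common to both and does not arise from the contradiction.

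**The case against.** The best defence is that this is a wording inconsistency in a secondary tolerance measure, and that its consequences are easily exaggerated. Several stronger inferences are tempting, and the document does not support them.

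- **That the diary is the only way AEs are found.** It is described as one mechanism beside self-report, and participants are encouraged to report any AE to the investigator. The schedule limits the days on which the score-3 rule can apply, not which AEs can be counted at all.
- **That the RS arms will look better tolerated than they are.** This requires that the shorter schedule is the one used, that severe symptoms fall on Days 4–7, and that they are not self-reported. None of these is established, and the diary form (Supplement 12) is not shown. Under-counting is possible, not demonstrated.
- **That the symptom comparison rests on Days 8–10 because of the shorter schedule.** It rests on those days under either schedule. The wording can fairly be read as the mean of whatever diary days fall in that week.
- **That by Day 8 women have adapted, or those who tolerated RS badly have stopped.** The document gives no time course of symptoms beyond the two-day adjustment and no frequency of early stopping. The Data management section allows data from women who withdraw to be used unless consent for that is withdrawn.

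There is also a separate GI symptoms questionnaire at Baseline, Day 10 and Day 56. It gives a second solicited measure of tolerance, but it is not tied to the score-3 rule and is not administered between Baseline and Day 10.

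These points limit the claim. They do not reconcile the two schedules.

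**Conclusion.** The contradiction stands: 20 recording days against 9, with Days 4–7 and 47–53 in dispute. If the shorter schedule is followed, the score-3 rule cannot operate on four consecutive days soon after RS begins. That is 4 of the 8 days from Day 3 to Day 10, or 4 of 7 if Day 3 is treated as baseline. Severe symptoms on those days would reach the AE count only by self-report, so the RS arms' severe GI events could be under-counted. The likely direction follows from the protocol's own statement about rapid introduction; the amount cannot be estimated from the document. The second-week wording is a separate, smaller fault present under both schedules. The matter concerns tolerance and AE ascertainment and should be corrected. It does not touch the primary outcome, the sample size or the glucose analyses.

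**What to change.** 1. State one diary schedule in both sections and in the participant materials, and apply it equally to all three arms. The daily window already given in the RS supplement section, Days 1–10 and 47–56, covers every day of the other schedule as well as the days now in dispute.
2. State that score-3 events are counted and reported by arm over that common window, with self-reported AEs collected alongside as already planned.
3. Separately, in the diary comparison, replace the reference to the second week with the days actually recorded, Days 8–10.

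The cost is a wording change and consistent diary instructions. Participants keep the diary for 11 more days than the Bowel symptoms record section asks (20 − 9) and none beyond what the RS supplement section already describes. For RS Diet and Control women this is a real, though small, added burden if the longer schedule was meant only for RS Supp. It is what makes the counts comparable between arms.

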##### RS supplement returned

Weighed portions of the RS supplement will be provided to participants fortnightly. Unconsumed RS supplement will be returned by participants and weighed on kitchen scales (Propert, China), to assess the percentage consumed and subsequent compliance with the RS consumption target.

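### Between diary windows, adverse events rest mainly on unprompted self-report in an open-label trial, and only RS Supp has fortnightly supplement exchanges, so ascertainment can differ between arms

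*Protocol article*

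**What the plan says.** All references are to the protocol article.

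- **AE routes.** Under Bowel symptoms record, the diary score is "one mechanism for identifying and rating adverse events (AE), along with participants self-reporting of AE". For the diary, "A score of 3 (severe) will be considered an AE and reported in the publications resulting from this trial". For self-report, "Participants will be encouraged to report any AE to the PI". No AE question at fixed times is described.
- **Diary days.** Bowel symptoms record states: "Participants will be asked to keep a bowel symptoms diary at Baseline (Day 1 to 3), Days 8 to 10 and Days 54 to 56". The RS supplement section states: "GI tolerance of the supplement will be measured via a daily bowel symptom diary for the first 10 days and Days 47 to 56". The two schedules differ.
- **Supplement exchanges.** The RS supplement section states: "Consumption and compliance of the RS supplement will be monitored by weight of unconsumed HAMS returned fortnightly". The section RS supplement returned adds: "Weighed portions of the RS supplement will be provided to participants fortnightly". By their nature these apply to RS Supp only. Their stated purpose is supply and compliance.
- **Contacts common to all arms.** Table 1 has clinic attendance on Days 1, 3, 10, 42 and 56, a reminder call or text on Day 28, and collection of samples and record data on Day 7 post-partum. It has no arm-specific visit. Recruitment adds supportive PI phone calls between widely spaced visits, without dates. The GI symptoms questionnaire is given at Baseline, Day 10 and Day 56.
- **Blinding.** Under Randomisation, neither participants nor investigators are blinded.

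**The concern.** When AEs are volunteered rather than asked for, the number recorded depends on how often a woman has an occasion to mention one and on what she expects to feel. Both can differ by arm here. RS Supp women have extra dealings with the study about the product itself, keep a daily supplement diary, and know that they take something expected to cause GI discomfort. Control and RS Diet women have no matching exchange.

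At stake is how the AE table will be read. Severe diary scores are to be published as AEs, GI tolerance is listed among the secondary outcomes, and readers of a three-arm report will set the counts side by side whether or not a test is attached. Unequal capture cannot be repaired after the data are in.

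**Working it through.** The plan gives no AE rate, capture probability or target figure, so there is nothing of its own to reproduce. The check is a count of days and contacts.

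**1. Days without a diary, up to Day 56**
- Bowel symptoms record: Days 1–3, 8–10 and 54–56 give 3 + 3 + 3 = 9 diary days. 56 − 9 = 47 days uncovered (84%).
- RS supplement section: Days 1–10 and 47–56 give 10 + 10 = 20 diary days. 56 − 20 = 36 days uncovered (64%).
- If the second schedule were meant for RS Supp only, that arm would have 20 diary days against 9. Scores of 3 could then be recorded on 11 more days in that arm alone.

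**2. Scheduled contacts after Day 10, up to Day 56**
- All arms (Table 1): Days 28, 42 and 56, so 3.
- RS Supp, calendar A (assumption: fortnights counted from the Day 3 supply): exchanges near Days 17, 31 and 45. Contact days are 17, 28, 31, 42, 45 and 56, so 6 against 3.
- RS Supp, calendar B (assumption: exchanges on Days 14, 28, 42 and 56, in line with Table 1): contact days are 14, 28, 42 and 56, so 4 against 3. On Day 28 the other arms have only a call or text.
- Calendar B is feasible on the stated supply. From Day 3, two days at 20 g use 40 g of the 600 g tub. The remaining 560 g lasts 560 / 40 = 14 days, so the first tub lasts 16 days, past Day 14. Each later tub lasts 600 / 40 = 15 days.

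If every contact had the same chance of picking up an event (assumption), the ratio of recorded events at equal true rates would be at most 6/3 = 2.0 under A and 4/3 = 1.3 under B. If exchanges prompt no reports, it is 1.0.

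**3. Illustration in cases**

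Assumptions: 30 women per arm, 20% with an AE on non-diary days (30 × 0.20 = 6 women), and 50% capture in the other arms (6 × 0.5 = 3.0 recorded).

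| Capture in RS Supp | Recorded, RS Supp | Recorded, each other arm |
|---|---|---|
| 50% (exchanges add nothing) | 3.0 | 3.0 |
| 70% | 4.2 | 3.0 |
| 90% | 5.4 | 3.0 |

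The result runs from no bias to nearly double, and depends wholly on an input that the article does not give.

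**4. What the common routes close**
- The questionnaire is common to all arms but leaves the time between Day 10 and Day 56 uncovered.
- The support calls are open to all arms but have no dates and no stated AE enquiry.
- The record review covers all arms. In Table 1 it sits at Day 7 post-partum, beside delivery, feeding and NICU items, and is unlikely to recover self-limiting GI symptoms at home.

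None of these closes the gap, though each narrows it.

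**The case against.** A reader might infer that AE capture is denser in RS Supp and that the AE comparison is biased against that arm, by about twofold. The documents do not support this, for five reasons.

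- **No stated link.** Nothing says that AEs are asked about at exchanges, that the PI handles them, or that they are separate visits. Recruitment says that study requirements are met at routine antenatal visits, so exchanges may coincide with visits that all women attend.
- **No planned test of AE counts.** The between-group tolerance comparison under Bowel symptoms record uses diary scores, the first two days against the second week. Neither it nor the questionnaire depends on the exchanges.
- **Even-handed counting.** The PI phone calls go to all arms and fall in the very gap at issue. They are not stated to be AE enquiries, but neither are the exchanges.
- **Other routes.** Women may report at any time, not only on contact days. All have antenatal care at the study hospital and a record review.
- **Article format.** AE scripts and exchange logistics are commonly left to a full protocol.

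Much of this stands. The twofold figure needs calendar A and equal capture at each contact, and the article gives neither. The direction is plausible but not shown. Two things remain. The article does state its AE method, and that method relies on unprompted reports with one arm having extra scheduled contact. It also states two diary schedules that conflict, which condensation does not explain.

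**Conclusion.** The point holds as a possible route to unequal ascertainment in the published AE data, not as a demonstrated bias. Outside the diary, for 36 to 47 of 56 days, capture rests mainly on unprompted reports to an unblinded PI, and only RS Supp has fortnightly exchanges.

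The size is unknown. The excess of scheduled contacts from Day 10 to Day 56 is between 4 v 3 and 6 v 3, on assumed calendars, and the effect on counts may be nil. After Day 56, Table 1 lists no further study contact before the post-partum collection. If exchanges continue with the supplement, RS Supp alone would have recurring study contact in that period, although all women still have routine antenatal care.

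The diary conflict is the firmer part. It is on the face of the text, and if the schedules differ by arm, diary-based AEs would be captured unequally too.

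**What to change.** 1. Ask the same short AE question in all three arms at the contacts already in Table 1: Days 10, 28, 42 and 56, and post-partum.
2. Make any between-arm AE summary primarily from those common contacts and the diary days common to all arms.
3. Report all AEs by arm as well. Show those volunteered at other times, including at supplement exchanges, by source. Do not drop them, because leaving them out could under-represent real events in the supplement arm.
4. Reconcile the diary days in the RS supplement and Bowel symptoms record sections, and state that the diary is the same in all arms.

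The cost is a scripted question at existing contacts, a source field on the AE form and a few sentences of text. No visit is added. The downside is a little more PI time.
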